## Abstract

**Background:**

Atrial fibrillation (AF) is a common arrhythmia, which is closely related to cardiovascular morbidity and mortality. Although acupuncture is used in the treatment of AF, the evidence is insufficient. The objective of this pilot trial is to evaluate the feasibility, preliminary efficacy, and safety of acupuncture in reducing AF burden for persistent AF after catheter ablation (CA).

**Methods and design:**

This will be a multi-center, 3-arm, pilot randomized controlled trial in China. Sixty patients in total will be randomly assigned to the specific acupoints group, the non-specific acupoints group, or the non-acupoints group in a 1:1:1 ratio. The whole study period is 6 months, including a 3-month treatment period and a 3-month follow-up period. All patients will receive 18 sessions of acupuncture over 12 weeks after CA and appropriate post-ablation routine treatment. The primary outcome is AF burden at 6 months after CA measured by electrocardiography patch that can carry out a 7-day continuous ambulatory electrocardiographic monitoring. The secondary outcomes include AF burden at 3  months after CA, recurrence of AF, quality of life, etc. The adverse events will also be recorded.

**Discussion:**

This pilot study will contribute to evaluating the feasibility, preliminary efficacy, and safety of acupuncture in reducing AF burden for persistent AF after CA. The results will be used for the sample size calculation of a subsequent large-scale trial.

**Trial registration:**

Chinese Clinical Trial Registry ChiCTR2000030576. Registered on 7 March 2020.

**Supplementary information:**

**Supplementary information** accompanies this paper at 10.1186/s13063-020-04967-y.

## Background

Atrial fibrillation (AF), as a common arrhythmia, increases in prevalence with advancing age [1]. Patients with AF have a 4–5 times greater risk of ischemic stroke than non-AF patients [2], resulting in 20% mortality and 60% disability when a stroke occurs [3]. AF triples the risk of heart failure [4] and doubles the risk of myocardial infarction [5]. In addition, AF is associated with a decreased quality of life and depression [6].

Catheter ablation (CA) is an invasive procedure used to treat AF that uses radiofrequency or other energy sources to isolate portions of the left atrium, such as the pulmonary veins, and other areas. For paroxysmal AF, although outcomes have improved over the last 20 years, success rates of CA, defined as freedom from recurrent AF, have plateaued in the 60–70% range [7]. For persistent AF, success rates are even more unfavorable at 45 to 60% at 1 year [8, 9]. There remain unmet needs in improving the ability to restore and sustain sinus rhythm [6]. Acupuncture, as a nonpharmacologic therapy, has been widely applied in cardiovascular diseases [10–12]. Acupuncture plays a role in regulating the autonomic nervous system in the treatment of many diseases [13–15]. The prevention effect of acupuncture on the recurrence of AF may have been achieved in this way. Previous trials have indicated that acupuncture could prevent persistent AF recurrence after electrical cardioversion or CA [16, 17]. However, in these trials, only the recurrence rate was evaluated, and there was no quantitative index like AF burden (the percentage of time in AF during a monitoring period) [18] and quality of life assessment was overlooked. Through a relatively simple detection method, the recurrence rate may be underestimated. Both are single-center studies, which could result in bias. As for the control setting, the blinding method cannot be completely achieved and the accurate efficacy of acupuncture was unable to be measured in the studies. Therefore, it is difficult to draw sound conclusions from the results of these trials due to the existing limitations of their design. In this context, we designed a multi-center, placebo-controlled pilot randomized trial to evaluate the feasibility, preliminary efficacy, and safety of acupuncture. AF burden will be the primary outcome and the recurrence rate will be measured by a relatively superior detection method.

It is well known that the efficacy of acupuncture is related to the acupoints selected. Some acupoints are called specific acupoints in traditional Chinese medicine (TCM), which have special properties, therapeutic effects, and a specific name [19, 20]. Specific acupoints have been applied in the treatment of many diseases [10, 21, 22], which are believed to be a group of acupoints superior to others in treating specific diseases. The aim of our study is as follows: (i) to explore the feasibility and provide power calculations for a future large-scale clinical trial, (ii) to explore the efficacy and safety of acupuncture as adjunctive therapy of routine care in reducing AF burden among patients with persistent AF after CA, and (iii) to examine whether the specific acupoints are superior to either non-specific acupoints or non-acupoints in therapeutic efficacy.

## Methods/design

### Study design

This multi-center, 3-arm, assessor and statistician blinded, pilot randomized controlled trial (RCT) will be conducted at four centers in China: Dongzhimen Hospital Affiliated to Beijing University of Chinese Medicine; Peking University People’s Hospital; The First Affiliated Hospital of Nanjing Medical University; Tianjin University of Traditional Chinese Medicine. Eligible patients will be enrolled from inpatient units of the cardiology departments at these hospitals. The whole study period will be 6 months and consist of a 3-month treatment period and a 3-month follow-up period. The CONSORT statement [23] and STRICTA guidelines [24] for acupuncture studies have been used as a framework for the methodology in this study. Besides, this protocol is reported following the SPIRIT guidelines (Additional file 1) [25]. The flowchart of this study is shown in Fig. 1.

**Fig. 1 Fig1:**
[figure not shown]
Flowchart of trial procedures

### Participants

Patients with persistent AF will be diagnosed according to the 2016 ESC guidelines [6]. Persistent AF is defined as AF that lasts for more than 7 days, including episodes that are terminated by cardioversion after 7 days or more [6].

#### Inclusion criteria

Persistent AF lasting no more than 3 years.Age between 18 and 75 years old (male or female).No acupuncture treatment within the previous 6 months.

#### Exclusion criteria

Severe heart failure (New York Heart Association class III or IV).Echocardiographic parameters: left ventricular ejection fraction < 40%, left atrium diameter > 5.0 cm.Severe lung, liver, kidney disease, or other serious primary diseases.Skin allergy to electrode patches for electrocardiographic monitoring.The estimated life expectancy of < 1 year.

### Ablation procedure

Physicians who perform ablations are required to have done 100 cases prior to this trial. All centers will cooperate with a relatively uniform standard of ablation procedures. All antiarrhythmic drugs (AADs), except amiodarone, will be discontinued for at least five half-lives before the procedure. Amiodarone will be recommended to be discontinued 3 months before the ablation procedure. Warfarin or novel oral anticoagulants should be taken for at least 3 weeks before CA. Transesophageal echocardiography will be performed on the day of CA or 1 day before CA to rule out left atrial thrombus.

All patients will undergo pulmonary vein isolation (PVI) by radiofrequency ablation. Selection of the type of ablation catheter, settings of power and irrigation, and the use of 3-dimensional mapping systems will be at the discretion of the physicians performing CA. It is regarded as an endpoint that the complete entrance and exit block of all pulmonary vein antra are confirmed in PVI. If the patient is still in a state of AF after PVI, electrical cardioversion will be performed. Patients who fail to be converted to sinus rhythm after PVI or electrical cardioversion will be excluded from this study.

### Randomization and blinding

All the patients will be randomly assigned (in a 1:1:1 ratio) to the specific acupoints (SA) group, non-specific acupoints (NSA) group, or non-acupoints (NA) group. NA group is the control group in this trial. Stratification will be performed by center and the method of block randomization will be applied in each center. An independent statistician who is not involved in treatment and outcome assessment will be in charge of computer-generated randomization sequence using SAS 9.3 software (SAS Institute, Cary, NC, USA). The allocation schedule will be carried out by an independent researcher who will be responsible for providing random numbers and group assignments to recruiters at each center through a centralized telephone randomization procedure. The patients, outcome assessors, and statisticians will be blinded. However, the acupuncturists will not be blinded due to the nature of acupuncture. The allocations will not be revealed until the data’s statistical analysis is completed.

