##### Atrial Fibrillation Effect and Quality of Life Scale (AFEQT)

The AFEQT [30] is a questionnaire specially designed to assess the quality of life in atrial fibrillation patients. The assessment will take place at baseline and 3 and 6 months. A summary score and subscale scores in the following 3 domains: symptoms, daily activities, and treatment will be calculated. Summary and subscale scores range from 0 to 100 (complete to no AF-related disability).

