### Sample size

The purpose of this pilot study is to evaluate the efficacy and safety of acupuncture in the treatment of AF and the feasibility for a further large-scale clinical trial. We did not find a suitable reference to calculate the sample size, but a minimum sample size of the clinical trial with 20 patients per group is used instead [32]. A total of 60 patients will be randomly assigned equally to SA, NSA, or NA group. This trial will provide data for sample size calculations of a future large-scale RCT.

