### Statistical analysis

Baseline characteristics will be summarized by the treatment group. Continuous variables will be described as mean ± standard deviations (normal distribution), or medians and interquartile ranges (non-normal distributions). Analysis of variance (ANOVA) or Kruskal-Wallis test (if normality is violated) will be applied in the comparison among three groups. Categorical variables will be described as frequency (percentage) and compared by *χ*^2^ test or Fisher’s exact test etc. As for the primary outcome, AF burden is expressed in the form of a percentage, which specifically refers to the proportion of time in AF within 7-days’ long for one patient in this study (range 0–100%). The null hypothesis that AF burden would be equivalent among the three arms (H0: effect of SA =effect of NSA = effect of NA) will be tested. The means of AF burden at 6 months of the three arms will be compared using ANOVA based on the preliminary assessment of the data distributions. If the ANOVA test among 3 arms is significant, the pairwise comparison will be performed by the least significant difference (LSD) test, and mean differences of pairwise comparison will be reported as effect measure. If AF burden is a skewed distribution, the data will be transformed to a normal distribution by corresponding methods for further comparison, and the same statistical analysis strategy will be adopted. The comparisons of AF recurrence between the three arms at 6 months will be performed based on a time-to-first-event analysis using the log-rank test. Kaplan-Meier cumulative AF recurrence rates will be calculated for each arm, with event or censoring times measured from the time of randomization. Hazard ratios (HRs) with associated 95% CIs will be derived using the Cox proportional hazards model.

All efficacy analyses will be based on the intention-to-treat principle. Missing data on the primary outcomes will be imputed by multiple imputations. An independent statistician who is blinded will conduct the statistical analysis using SAS 9.3. We will set a significance level of *P* < 0.05 (two-sided) without adjustment on account of the values considered explorative.

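### Randomisation is stratified by center, but no efficacy analysis named in the protocol uses center; if center is prognostic, the AF-burden ANOVA loses some precision that is almost free to recover

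*Protocol article*

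**What the plan says.** **Design.** The Study design section of the protocol article says the trial "will be conducted at four centers in China". The Randomization and blinding section gives a 1:1:1 ratio and adds: "Stratification will be performed by center and the method of block randomization will be applied in each center". On size, the Sample size section says "We did not find a suitable reference to calculate the sample size" and that "a minimum sample size of the clinical trial with 20 patients per group is used instead", so 60 in total.

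**AF burden (primary).** The Statistical analysis section says that the six-month means "of the three arms will be compared using ANOVA based on the preliminary assessment of the data distributions". LSD pairwise tests follow a significant result, with pairwise mean differences as the effect measure. There is a transformation fallback for skewed data, and multiple imputation for missing values. Center does not appear.

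**Recurrence.** The method is a "time-to-first-event analysis using the log-rank test", with Kaplan-Meier rates and Cox hazard ratios with 95% intervals. No strata or covariates are named.

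**AFEQT.** Of the questionnaire, its own section says "The assessment will take place at baseline" and again at 3 and 6 months. The Statistical analysis section never mentions AFEQT. The only rule there that could reach it is the general one for continuous variables, ANOVA or Kruskal-Wallis across three groups, which directly follows the sentence on baseline characteristics and uses no covariate.

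The text schedules AF burden only at 3 and 6 months, so it describes no baseline burden to adjust for.

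**The concern.** Blocking within center balances the arms inside each center, so differences between centers largely cancel out of the comparison of arm means. A one-way ANOVA does not know this and leaves the between-center variation in the residual. If centers differ in outcome, the standard error of the mean differences is overstated, the test rejects less often than 5% under the null, and power is lost. Some center effect is plausible, because the Ablation procedure section leaves catheter type, power and irrigation settings, and mapping system to the operating physician.

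For this trial the stake is mainly precision. The Abstract, Background and Sample size sections all say the results will feed the sample size of a larger trial, and the Discussion says the comparison of the two real-acupoint arms will decide which point selection goes forward. A residual SD that includes center variance is larger than the SD relevant to a center-adjusted future trial.

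**Working it through.** **Inputs from the protocol:** 4 centers, 3 arms, 3 × 20 = 60 patients, two-sided 5% level. The total agrees with the stated 60. No effect size, SD or power is given, so there is no power figure to reproduce.

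**Assumed, because the documents do not give them:** equal centers (15 patients, 5 per arm), normal outcome with total within-arm SD of 1, ICC from 0 to 0.20, an effect of 0.8 SD in one arm, and a correlation of 0.3 to 0.7 between baseline and follow-up AFEQT.

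**1. AF-burden ANOVA, by formula.** Let r be the ICC.

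- One-way residual: 60 − 3 = 57 df, of which 3 belong to center. Expected residual sum of squares = 57(1 − r) + 15 × 3 × r, so expected mean square = (1 − r) + 45r/57 = 1 − 0.2105r.
- Variance that actually applies to the arm contrast: 1 − r, estimated on 57 − 3 = 54 df once center is fitted.
- Variance overstatement = (1 − 0.2105r)/(1 − r). Interval-width ratio = its square root × t(57)/t(54) = square root × 2.0025/2.0049.

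| r | Variance ratio | Width ratio |
|---|---|---|
| 0.05 | 0.9895/0.95 = 1.042 | 1.019 |
| 0.10 | 0.9789/0.90 = 1.088 | 1.042 |
| 0.20 | 0.9579/0.80 = 1.197 | 1.093 |

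**2. AF-burden ANOVA, by simulation** (40,000 trials per setting; three-arm F test; power for the 0.8 SD effect).

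| ICC | Type I error, no center | Type I error, center | Power, no center | Power, center | 95% CI half-width in SD, no center / center |
|---|---|---|---|---|---|
| 0 | 5.1% | 5.0% | 72.4% | 72.2% | 0.630 / 0.630 |
| 0.02 | 4.8% | 5.0% | 72.6% | 73.2% | 0.629 / 0.624 |
| 0.05 | 4.5% | 5.0% | 73.0% | 74.5% | 0.627 / 0.615 |
| 0.10 | 3.8% | 4.8% | 73.8% | 77.1% | 0.623 / 0.599 |
| 0.20 | 3.0% | 4.8% | 74.9% | 81.8% | 0.615 / 0.565 |

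The half-width ratios at ICC 0.05, 0.10 and 0.20 are 1.020, 1.040 and 1.088, in line with the formula. The power differences, from unrounded values, are 1.6, 3.3 and 6.9 points.

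**3. Recurrence** (about 1,500 trials per setting; about half the control patients with an event; log hazard ratio −1.2 in one arm). Power of unstratified against center-stratified log-rank:

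- no center effect: 56.7% against 56.3%;
- center log-hazard SD 0.3: 54.4% against 55.2%;
- center log-hazard SD 0.6: 49.4% against 55.0%.

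The mean standard error of the log hazard ratio at SD 0.6 is 0.635 unstratified and 0.643 stratified, so it does not shrink.

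**4. AFEQT with baseline as covariate.** The variance factor is 1 − ρ² and the equivalent total N is 60/(1 − ρ²). Pairwise power for a 0.8 SD difference without the covariate is 70.1% (57 df). The last two columns use 56 df, with baseline only.

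| ρ | Variance cut | Equivalent N | CI width ratio | Power |
|---|---|---|---|---|
| 0.3 | 9% | 66 | 0.954 | 74.1% |
| 0.5 | 25% | 80 | 0.866 | 81.9% |
| 0.7 | 49% | 118 | 0.714 | 93.6% |

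**The case against.** **Silence is not a statement.** The article does not say the analyses omit center; its phrase about no adjustment concerns the significance level. Model terms are often left to an analysis plan. This stands in part. However, the article fixes the primary test down to its post-hoc procedure, transformation and imputation, and the test so described does not match the randomisation it describes.

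**The center effect may be small.** The Ablation procedure section also asks for a broadly common standard, with pulmonary vein isolation and one block endpoint for all patients. The Interventions section adds trained acupuncturists and standard prescriptions. As an illustration, the Background quotes 45 to 60% one-year success in persistent AF. If two centers sat at each end, center would explain 0.075²/(0.525 × 0.475) = 0.0056/0.249 = 2.3% of the variance in a binary outcome. Those figures do not come from these centers, but they show that a share near 2%, with little loss, is quite possible. This stands, and the size must be stated as conditional.

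**The model is idealised.** AF burden is bounded at 0 to 100% and may be skewed, and center sizes need not be equal. This stands: the figures are indicative.

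**Stronger readings that the documents do not support:**

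- *That power is certainly lost.* No ICC is given, and at zero the loss is nil.
- *That hazard-ratio intervals are too wide.* Stratifying by center did not reduce the standard error of the log hazard ratio.
- *That the AFEQT comparison ignores its baseline.* No AFEQT analysis is stated. One can say only that no baseline-adjusted analysis is named and the one general rule is unadjusted.
- *That each center has its own acupuncturists*, as a source of center effects. The protocol does not say so.

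**Conclusion.** The point holds as a conditional, modest loss of precision. The allocation is stratified by center and none of the named efficacy methods uses center. For AF burden, under the normal, equal-center assumptions, the cost runs from nothing (ICC 0) through under 1 point of power (ICC 0.02) to about 7 points with intervals about 9% too wide (ICC 0.20). The error is on the conservative side, the mean differences stay unbiased, and no stated power figure is contradicted, since the sample size was not powered and the tests are called exploratory.

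The most lasting consequence is for planning. At ICC 0.05, 0.10 and 0.20 the unadjusted variance, and with it the sample size of a center-adjusted successor trial, would be overstated by about 4%, 9% and 20%. For recurrence, any gain is in test power and appears only when centers differ strongly. For AFEQT the possible gain is larger, but it rests on an assumed correlation and on an analysis the article does not spell out.

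**What to change.** 1. **AF burden:** add center as a fixed factor to the ANOVA and to the LSD comparisons. Keep the mean difference as the effect measure; a stratified rank test would not itself supply it. Report the center-adjusted residual SD for planning the next trial.
2. **Recurrence:** stratify the log-rank test and the Cox model by center.
3. **AFEQT:** state that the 3- and 6-month scores are analysed by ANCOVA with baseline AFEQT and center.

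The cost is 3 of 57 residual degrees of freedom for center, about 0.2 points of power if center does not matter at all, plus 1 degree of freedom for baseline AFEQT. No extra data are needed, because center is known and baseline AFEQT is already scheduled. The wording should be settled before allocations are revealed.

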##### Blinding assessment

Blind evaluation will be conducted in order to evaluate whether the blind method is successful. After treatments in weeks 6 and 12, all patients will be asked to guess whether the needles go deep or shallow layers in the acupuncture treatment they receive. Before the treatment, one or two doctors of each center will be in charge of recruiting the patients and gaining informed consent from them. The patients will be informed: “There are three different groups of acupuncture with three different acupoint selection schemes. You are equally likely to be assigned to all three groups, and previous studies have shown that all three methods were associated with positive outcomes in clinical studies.”

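### Group assignments are telephoned to the doctors who recruit and obtain consent within center blocks, which weakens allocation concealment and conflicts with the protocol's own statement on when allocations are revealed

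*Protocol article*

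**What the plan says.** All of this is in the protocol article.

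- **Method.** Randomization and blinding: "Stratification will be performed by center and the method of block randomization will be applied in each center". The ratio is 1:1:1 across three arms.
- **Who is told.** The same section makes an independent researcher responsible for "providing random numbers and group assignments to recruiters at each center through a centralized telephone randomization procedure". The message therefore carries the group as well as the number.
- **Who the recruiters are.** Blinding assessment: "one or two doctors of each center will be in charge of recruiting the patients and gaining informed consent from them".
- **Who is blinded.** Randomization and blinding: "The patients, outcome assessors, and statisticians will be blinded". It then says: "However, the acupuncturists will not be blinded due to the nature of acupuncture". Recruiters are in neither list.
- **When allocations are revealed.** The same section ends: "The allocations will not be revealed until the data’s statistical analysis is completed".
- **Size.** Sample size gives 60 patients, 20 per arm. Study design gives four centers.

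**The concern.** Central telephone randomization protects enrolment because the person enrolling cannot know which arm comes next. Blocking weakens that protection for anyone who knows the earlier assignments in the stratum, because each block must balance and the remaining places are constrained. Here the call that conceals the next assignment also hands over the history of the sequence, and it goes to the few people who approach patients and take consent.

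A recruiter who suspects the next arm could, knowingly or not, hold back or press a borderline patient, or present the trial differently. Some eligibility criteria leave room for judgment, such as other serious primary disease and estimated life expectancy. With 20 patients per arm, a few steered enrolments could shift mean AF burden. The Sample size and Discussion sections say that this trial will supply data for the later trial's sample size and will guide its choice of acupoint scheme.

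Separately, the section contradicts itself. Allocations cannot both be telephoned to recruiters at enrolment and remain unrevealed until the analysis is complete. Only the acupuncturist needs the group.

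**Working it through.** The plan states no figure on predictability, so there is nothing to reproduce. The check asks how well a recruiter could guess.

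**Inputs from the protocol:** three arms at 1:1:1 (chance = 1/3 = 33.3%); blocks within center; group disclosed to recruiters; 60 patients; four centers.

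**Assumptions:** block size (not stated, so a range is shown); one recruiter sees every past assignment in the center; equal recruitment, giving 60 / 4 = 15 patients per center.

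**Formula.** With a, b and c places left in the current block for the three arms, the best guess is the arm with most places left. It is right with probability max(a, b, c) / (a + b + c). Average this over all positions and all possible histories in the block.

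**Block of 3.** The success probabilities at positions 1 to 3 are 1/3, 1/2 and 1. The mean is (0.3333 + 0.5 + 1) / 3 = 1.8333 / 3 = 0.611.

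**Block of 6.** The expected success at positions 1 to 6 is 0.3333, 0.4, 0.5, 0.5333, 0.6 and 1. The mean is 3.3667 / 6 = 0.561. The assignment is certain at position 6 always and at position 5 with probability 1/5, so the share known with certainty is 1.2 / 6 = 20.0%.

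**Exact enumeration, fixed block of known size:**

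| Block size | Best guess correct | Known with certainty | At least one arm ruled out |
|---|---|---|---|
| 3 | 61.1% | 33.3% | 66.7% |
| 6 | 56.1% | 20.0% | 46.7% |
| 9 | 53.2% | 14.3% | 35.7% |
| 12 | 51.2% | 11.1% | 28.9% |
| 15 | 49.7% | 9.1% | 24.2% |

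For a center of 15 patients this means 15 × 0.611 = 9.2 correct guesses with blocks of 3, or 15 × 0.497 = 7.5 with one block of 15. Chance gives 15 / 3 = 5.0.

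**Recruiter who does not know the block size** and simply guesses the least-used arm so far (simulation, 15 patients per center, 100,000 runs):

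| Scheme | Correct |
|---|---|
| fixed 3 | 61.1% |
| fixed 6 | 53.1% |
| fixed 9 | 49.1% |
| varying 3/6 | 56.8% |
| varying 3/6/9 | 54.0% |
| varying 6/9 | 52.7% |

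Hiding or varying the block size therefore does not bring the guess back to chance. If the recruiter receives no group codes, there is no history to use and the rate is 1/3 = 33.3%.

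**The case against.** The safeguards that are in place are real. An independent statistician generates the sequence, an independent researcher releases it centrally, and the next assignment is hidden until the call. Many eligibility criteria are fixed or measured, and all three arms are needled, which limits both the motive and the room for selective enrolment. With two recruiters in a center, each sees only part of the sequence unless they share what they know, so the rates above would be lower. The trial is a pilot with P values described as explorative. All of this stands and limits the size of the problem. It does not remove it, because the protocol expressly sends the group to the enrolling doctors.

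The sentence on revealing allocations could be read narrowly, as covering only the blinded roles, since the acupuncturists must know the group in any case. On that reading recruiters still have no stated status, so the section still needs reconciling.

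Three stronger readings are tempting but not supported.

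- **Every third patient's arm is known before consent.** This needs fixed blocks of 3 and a recruiter who knows it. The article gives no block size. It may properly be withheld from the centers and left to the full protocol, so its absence is not a fault.
- **Cardioversions, repeat ablations and AF-related hospitalizations are biased by unblinded care.** Nothing says that recruiters manage patients after ablation. Their stated role is recruitment and consent. Enrolment from cardiology inpatient units makes an overlap possible but does not show it.
- **Outcome assessment is unblinded.** Recruiters are not said to assess outcomes. Assessors are stated to be blinded, and the patch recordings are read by algorithm and reviewed by technicians.

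**Conclusion.** The point holds as a weakness in allocation concealment and an internal conflict in Randomization and blinding. It rests on a stated rule, not on missing detail. The conflict and the disclosure to recruiters follow from the text without any calculation.

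For a recruiter who sees all earlier assignments in the center, the best guess is right about 50% to 61% of the time for known fixed blocks of 15 down to 3, and about 49% to 61% under the schemes tried when the block size is unknown. Chance is 33%. The assumptions are the block size, one recruiter seeing every assignment and, for the simulations and the counts per center, about 15 patients in each. Certainty about the next arm applies to a minority of patients, 9% to 33% for known fixed blocks.

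These are guess rates, not estimates of bias in AF burden, and the documents do not allow one. Performance bias remains conditional on recruiters also managing care after ablation. The correction should be made, because it is simple and the exposure serves no purpose.

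**What to change.** Change Randomization and blinding as follows:

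1. After consent and baseline assessment, the recruiter reports eligibility by telephone and receives only a patient number.
2. The independent researcher sends the group directly to the acupuncturist, who is already unblinded.
3. Recruiters are added to the blinded roles.
4. The sentence on when allocations are revealed is reworded to agree, with the acupuncturists and the independent researcher as the stated exceptions.

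The cost is a different call recipient and one line in the procedure, with no added staff, patients or visits. Trial status says that recruitment is under way, so the change protects remaining enrolment only. Recruiters keep what they already know, which can inform guesses until any part-filled block is complete. The report should state how many patients were enrolled under the present rule.
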